## **E. RESEARCH DESIGN**

### **E1. Study design and setting**

The study is a randomized-controlled trial to be conducted at the outpatient Supportive Care Center at the University of Texas MD Anderson Cancer Center. We plan to enroll 136 patients and up to 136 caregivers. Up to 20 physicians will be enrolled. Each physician may see up to 15 patients in this study.

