### **E3. Randomization**

Participating patients will be randomized in a double-blind fashion into one of two treatment groups: the active group will receive the QPS intervention and the control group will receive the GIS intervention. Randomization will be conducted via the Clinical Trial Conduct website developed by the Department of Biostatistics. We will randomize patients using Pocock-Simon's method and the randomization will be stratified by "physician" in order to carefully control for physicians' impact on patients' perception of helpfulness (primary endpoint).

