During the patient-physician encounter, the physician will be asked to endorse question asking. Physician endorsement of question asking will be defined according to the following standardized protocol: 1) The physician asks the patient/ caregiver if they have any questions; and either 2) explains why it is important to ask questions, or 3) invites the patient/caregiver to ask questions more than once. The conversation will be recorded with a voice recorder and later transcribed. The audio-recordings will be sent via Box.com to Landmark Associates Inc. to be transcribed professionally. At the end of the consultation, the research staff who will be absent during the conversation, will ask the patient to complete the Spielberger State Trait Anxiety Inventory (**Appendix A**) again, the questionnaires assessing patients'/caregivers' views about the information material (**Appendix F**) and overall satisfaction with consultation (**Appendix G**). The questionnaires should take about 13 minutes to complete. The participating caregiver will also separately complete **Appendix F**. It should take about 5 minutes to complete. All the information materials will be collected from the participants after the consultation but those who indicate the desire to keep them will be given a copy of their forms for future use. At the end of the study, all study patients will receive a patient information booklet which also contains the GIS content. This is part of usual practice in the clinic and it will ensure that all patients get to receive identical standardized clinical care. The physician will also be asked to complete a physician assessment questionnaire (**Appendix H**) after the clinic encounter. This should take about 2 minutes to complete.

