For the primary objective and secondary objectives 2, 3, 4, 8, two sample t-test or Wilcoxon rank sum test, whichever appropriate, will be used to compare a) patients'/caregivers' perception of helpfulness in communicating with their physicians, b) patients'/caregivers' overall satisfaction with the consultation, c) physician's view/overall satisfaction about the information material and d) the change in patient anxiety state scores before and after consultation between the QPS and the GIS. For the secondary objective 5, two sample t-test or Wilcoxon rank sum test, whichever appropriate, will be used to compare the average speaking time of patient or physician during the consultation visit. Also, general linear model will be applied to assess the effect of QPS on the average speaking time adjusting for clinically and/or statistically important factors. For the secondary objective 6, univariate/multicovariate logistic regression will be used to evaluate patients' demographic and clinical factors on patients' perception of helpfulness of QPS when dichotomizing the answer to the question 3 in Appendix F ("Agree/Strongly Agree"=Helpful vs the rest). For the secondary objective 7, we will estimate the preference of information material with 95% confidence intervals. Also, univariate/multicovariate logistic regression will be used to evaluate patients' demographic and clinical factors on overall patients' preference between QPS and GIS.

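### Randomisation is stratified by physician but the between-arm tests leave physician out, so they are conservative and lose precision, mainly for the physicians' own ratings

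*Protocol*

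**What the plan says.** Section E3 randomises individual patients by the Pocock-Simon method with physician as the stratification factor. Its stated reason is "in order to carefully control for physicians' impact on patients' perception of helpfulness (primary endpoint".

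Section E1 sets the number of physicians and their load: "Up to 20 physicians will be enrolled" and "Each physician may see up to 15 patients in this study".

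Section F names the between-arm test objective by objective: "For the primary objective and secondary objectives 2, 3, 4, 8, two sample t-test or Wilcoxon rank sum test, whichever appropriate". The outcomes covered include the "physician's view/overall satisfaction about the information material". Section E6 collects that rating after each encounter: "The physician will also be asked to complete a physician assessment questionnaire". One physician therefore contributes several ratings.

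The only adjusted between-arm model is for objective 5, where a "general linear model will be applied to assess the effect of QPS on the average speaking time adjusting for clinically and/or statistically important factors". Physician is not named among those factors. The power statement in section F also rests on a plain two-group t-test.

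**The concern.** Section E3 treats physician as prognostic for the primary endpoint and restricts the randomisation accordingly. Section F then analyses the data as if that restriction had not been made. Balancing arms within physician takes most of the between-physician variation out of the estimated difference. An unadjusted test still counts that variation as error, so its standard error no longer describes the estimator, and its confidence intervals and p-values do not match the design.

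Objective 4 is the clearest case. The outcome is a score given repeatedly by a small group of raters, and each rater's habits are likely to show in every score. Both named tests treat those scores as independent. What is at stake is precision and agreement between design and analysis, not the validity of a positive result.

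**Working it through.** **Inputs from the protocol.** 136 randomised 1:1, 128 evaluable, 5% attrition, difference 2, common SD 4, two-sided 0.05, 80% power (section F). At most 20 physicians and 15 patients each (section E1).

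**Input not in the protocol.** The ICC for physician. It is an assumption throughout and is shown as a range.

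**1. The stated figures.** With 64 per arm, SE = 4 × √(2/64) = 0.707 and the standardised difference is 2/0.707 = 2.83. Power is 80.7% by the normal approximation and 80.1% by the noncentral t. Attrition: 128/0.95 = 134.7, so 135 against 136 stated. The figures reproduce, as a calculation with no physician term.

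**2. Ratings per physician.** 136/15 = 9.07, so at least 10 physicians are needed. With 10 there are 13.6 patients each on average; with 20 there are 6.8.

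**3. Direction of the error.** With arms balanced within physician, the true SE is about 0.707 × √(1 − ICC), while the unadjusted test reports about 0.707. The ratio is 1/√(1 − ICC): 1.010, 1.026, 1.054, 1.195 and 1.414 at ICC 0.02, 0.05, 0.10, 0.30 and 0.50. Example at ICC 0.2: 0.707 × √0.8 = 0.632. Simulation with 10 physicians gives a true SD of 0.63 and a mean reported SE of 0.70.

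**4. Simulation with near-exact balance within physician.** 128 patients, total SD 4, 10,000 runs per setting. The comparator is a linear model with physician fixed effects. Where two figures are given they are for 10 / 20 physicians.

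| ICC (assumed) | Type I error, unadjusted | Power, unadjusted | Power, adjusted |
|---|---|---|---|
| 0 | 4.7% / 4.7% | 80.1% / 80.3% | 79.9% / 79.6% |
| 0.05 | 4.8% / 4.3% | 80.8% / 80.5% | 81.9% / 81.8% |
| 0.1 | 4.3% / 4.5% | 81.6% / 81.7% | 84.3% / 83.7% |
| 0.2 | 2.8% / 3.2% | 83.2% / 82.8% | 88.1% / 87.9% |
| 0.3 | 2.4% / 2.1% | 84.8% / 84.2% | 91.5% / 91.8% |
| 0.5 | 1.2% / 1.0% | 88.6% / 86.9% | 97.8% / 97.5% |

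The adjusted model's type I error stays between 4.7% and 5.8%.

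**5. Simulation closer to the planned allocation.** Minimisation on physician, 136 randomised and 128 evaluable, again with physician fixed effects as comparator. For ICC 0.02 to 0.10: deterministic allocation, 4,000 runs, Monte Carlo error about 0.6 points.

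| ICC (assumed) | 10 physicians, unadjusted v adjusted power | 20 physicians, unadjusted v adjusted power |
|---|---|---|
| 0.02 | 81.0% v 81.0% | 80.5% v 79.3% |
| 0.05 | 80.3% v 81.4% | 80.5% v 81.3% |
| 0.10 | 82.3% v 84.7% | 80.4% v 82.0% |

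Unadjusted type I error is 4.2% to 5.1%. The change in power runs from 79.3 − 80.5 = −1.2 to 84.7 − 82.3 = +2.4 points.

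At ICC 0.3, type I error is about 2.5% and power about 83-86% against 91-92%. At ICC 0.5 they are about 1% and 86-89% against 98%. For objective 4 the 0.5 SD effect (2/4) is borrowed from the primary endpoint, since the protocol states no effect for physicians' ratings.

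**The case against.** The strongest case on the other side has four parts.

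- **The primary endpoint is hardly affected.** This stands. At an assumed ICC of 0.02 to 0.10 the tests run close to their nominal level, and adjustment moves power by a point or two in either direction.
- **The larger figures rest on an assumed ICC.** This also stands. Nothing in the protocol supports 0.3 to 0.5 for physicians' ratings. Those values are plausible for repeated scores by one rater, but they remain an assumption and concern one secondary objective.
- **Balance may be looser than assumed.** Odd counts, attrition and an unstated assignment probability all weaken balance within physician and bring the unadjusted test nearer its nominal level. The minimisation runs allow for odd counts and attrition, and the conservatism remains at the higher ICCs. A random element in the assignment would weaken it further.
- **The analysis plan may add a physician term.** It may, but section F already names the test for each objective, and its closing allowance for other methods commits to nothing. A plan that followed the protocol would carry the mismatch forward.

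A reader might infer more than the protocol supports. Up to 15 patients per physician, treated as independent, looks like a cluster-trial error that inflates false positives and calls for a larger sample. It is not: patients are randomised individually within physician, so the error runs the other way. Nor does adjustment lift the primary power from 80% to 84% at ICC 0.10, because under the same design the unadjusted test already has about 80-82%. The closed-form ratio at ICC 0.5 implies a type I error near 0.6%, but it assumes exact balance and a fully captured between-physician variance; simulation gives about 1%. Finally, how to choose between the t-test and the rank-sum test is a separate matter that an analysis plan commonly settles, and it is not part of this point.

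**Conclusion.** The mismatch between design and analysis is in the protocol's own text and should be corrected. It is a matter of precision and consistency and does not threaten the trial's validity. The unadjusted tests are conservative, and the stated 80% power is kept provided the SD of 4 is the total SD, including between-physician variation.

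For patient-reported outcomes the effect is small over the assumed ICC range of 0.02 to 0.10. For physicians' ratings in objective 4 it could be material: at an assumed ICC of 0.3 to 0.5, roughly 5 to 12 points of power are given up (from 91 − 86 = 5 to 98 − 86 = 12) and the test runs at about 2.5% to 1% instead of 5%. Confidence is high in the mismatch and its direction. It is limited in the size, which depends on an ICC that the protocol does not give and on how closely the arms balance within physician. The figures are for 128 evaluable records; the number of caregivers is not fixed.

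**What to change.** In section F, state that the between-arm comparisons for the primary objective and for objectives 2, 3, 4 and 8 include physician, the stratification factor, as a random or fixed effect. A physician-stratified test such as van Elteren would also answer the point. Report the adjusted difference with its 95% confidence interval.

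For the primary objective the form of the model depends on a separate inconsistency. Section E9 defines the outcome as the proportion agreeing on item 3 of Appendix F, while section F uses the 0-10 score on item 4. If the score is kept, the linear or rank-based version applies. If the proportion is kept, use Cochran-Mantel-Haenszel stratified by physician, or logistic regression with a physician effect.

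The change is one of wording, since physician is already recorded for randomisation. It costs a few degrees of freedom and, with many physicians, an ICC near zero and fixed effects, up to about 1 point of power. No change in sample size is needed.

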## E6. Study Procedures

The research staff will first identify a potentially eligible candidate by screening all scheduled patient consultations on that day, and then inform and obtain a verbal consent from the attending physician for the patient's participation in the study. After the routine nurse assessment, the

research coordinator will obtain patient's written consent and then ask him/her to complete the Spielberger State Trait Anxiety Inventory (**Appendix A**), 2 questions from Cassileth Information Styles Questionnaire (**Appendix B**), and the Control Preferences Scale (**Appendix C**). The patient will then be randomized to receive either the QPS (**Appendix D**) or the GIS (**Appendix E**). It will take approximately 5 minutes to read through the QPS or GIS. The questionnaires should take about 5 minutes to complete. Caregivers accompanying patients to the clinic who are willing to participate in the study will also be asked to provide consent and will be given the same information material (either QPS or GIS). In a situation where more than one eligible caregiver is present, the one most involved in the patient's care, as determined by the patient, will be the first person to be approached. If he/she declines to participate, the next most involved caregiver identified by the patient will then be approached until there are no more eligible caregivers present.

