## **E9. Outcome measures**

### **1. Patients' perception of helpfulness in communicating with their physicians between a question prompt sheet (QPS) and a general information sheet (GIS).**

This will be assessed as the proportion of patients who agree or strongly agree that the information was helpful in the communication with their physician. It will be measured using the third item of the **Patients/ Caregivers Assessment Questionnaire** consisting of rating scales regarding the information material (**Appendix F**). Participants will rate the **perception of helpfulness** of the material using in a 5-point Likert scale from "strongly disagree" to "strongly agree" on item #3: "The material helped me to communicate with my doctor". It will also consist of 0 to 10 point scales assessing the extent to which the information material was helpful, was clear or easy to understand, had the right amount of information, was recommendable to other patients, did not make them anxious, enabled them to think of questions or concerns they hadn't thought of before, and a similar question sheet will be used by them before they see their doctor in the future. The questionnaire was developed from previous studies and through discussions between the authors. (J.A; E.B).

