**5. Effect of the QPS versus the GIS on the average speaking time of the patient or physician.**

This information will be extracted from the transcribed documents of the recording during the patient-physician clinical encounter. We will also measure the following outcomes from the same transcribed document:

- a) Total duration of the visit in minutes;
- b) Total number of questions asked by the patient and/or caregiver; and
- c) Categories of each question asked, namely: the palliative care team/services provided, symptoms and treatment, prognosis, end of life issues, or other.

**6. Association between the patient perception of helpfulness and demographic (age, gender, ethnicity, educational level, presence of a caregiver) and clinical characteristics (cancer stage, pre-consultation anxiety level, patient preferences for information, and patient preferences for involvement in decision-making).**

- a) Anxiety level will be measured by the ***Spielberger State Trait Anxiety Inventory*** (**Appendix A**) as described in Outcome #8 below.
- b) Patient preferences for information will be assessed using 2 items from the **Cassileth Information Styles Questionnaire** which assesses the amount of details and the type of information preferred by patients on a scale of 1 to 5. (**Appendix B**).

- c) Patient preferences for level of involvement in decision-making will be assessed using **The Control Preferences Scale**, a validated and reliable scale that measures patients' preferred level of involvement in decision-making during consultations with their physicians (**Appendix C**). The tool consists of statements describing different decision-making roles and patients are classified as preferring 'active', 'passive', or 'collaborative' roles in making decisions regarding their treatment based on their choices to those statements.

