### **F. STATISTICAL CONSIDERATIONS**

The primary outcome is patients' perception of helpfulness (0-10 scale) in communicating with their physicians after the first consultation visit (Appendix F, Question 4). At patient enrollment, randomization will be obtained via Clinical Trial Conduct website. A total of 136 patients will be randomized into 2 groups (QPS and GIS) in the ratio of 1:1 to reach 128 evaluable patients with 5% attrition rate due to withdrawal or lost to follow-up. With 128 evaluable patients, we will have 80% power to detect a difference in means of 2 assuming the common standard deviation of 4 using two group t-test with a two-sided significance level of 0.05. We will also reach out to patients' caregivers to collect information if available.

Standard statistics including mean, standard deviation, median, range, frequency and percentage will be summarized for variables of interest, such as patients' demographics, clinical characteristics, anxiety state, patients'/caregivers' views about the information material, patients' satisfaction, physicians' views about the information material and consultation, patients' preferences for information, patient preferences for level of involvement in decision-making and patients' overall preference between the QPS and the GIS at the follow-up visit. Two sample t- test or Wilcoxon rank sum test, whichever appropriate, will be used to compare continuous variables of interest between the QPS and the GIS. Chi-squared test or Fisher's exact test, whichever appropriate, will be used to test for associations between categorical variables and helpfulness of information material (helpful vs the rest) for each of the QPS and the GIS as well as the preference in types of information material (QPS vs GIS).

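### The primary comparison of the 0-10 helpfulness score is left as an unadjusted t-test or Wilcoxon with no selection rule: a valid analysis, but with no fixed effect measure and no use of scores collected before randomisation

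*Protocol*

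**What the plan says.** - **Outcome and sizing.** Section F states: "The primary outcome is patients' perception of helpfulness (0-10 scale) in communicating with their physicians after the first consultation visit". On sample size it says "With 128 evaluable patients, we will have 80% power to detect a difference in means of 2", with a common SD of 4, "using two group t-test with a two-sided significance level of 0.05".
- **Primary test.** Section F then gives the comparison as "For the primary objective and secondary objectives 2, 3, 4, 8, two sample t-test or Wilcoxon rank sum test, whichever appropriate". It does not say what makes one of the two appropriate, and it lists no covariates. The section closes by allowing other methods where appropriate, without tying any to the primary outcome.
- **Scores before allocation.** In section E6 the patient completes the anxiety inventory, two Cassileth items and the Control Preferences Scale. After that, "The patient will then be randomized to receive either the QPS" or the GIS.
- **Where those scores are used.** Section E9, outcome 6, relates perceived helpfulness to demographic factors and to "clinical characteristics (cancer stage, pre-consultation anxiety level, patient preferences for information, and patient preferences for involvement in decision-making". In section F they enter secondary logistic models, including one of dichotomised item 3.
- **Adjustment elsewhere.** Section F plans an adjusted linear model for speaking time, a secondary outcome, but none for the primary one.
- **Stratification.** Section E3 stratifies by physician to control the physician's influence on the primary endpoint. The primary test does not include physician.

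**The concern.** There are two separate matters.

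1. **The effect measure is open.** The t-test addresses a difference in means, which is what the trial is sized on. The Wilcoxon test addresses rank order and gives no mean difference. With both on offer and no rule, the quantity to be reported for the one confirmatory result is not settled. On a bounded 0-10 rating that bunches near the top, the two tests can also differ on significance.
2. **Baseline information goes unused.** If scores taken before randomisation predict the rating, adjusting for them narrows the interval with the same patients. The design has almost no spare power, so a gain of a few points would be useful.

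**Working it through.** **Inputs from section F:** difference 2, SD 4, two-sided 0.05, 128 evaluable, 1:1 (64 per arm).

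**Assumption:** R², the share of outcome variance explained by the baseline scores. The protocol gives no value, so a range of 0 to 0.20 is shown.

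**Step 1: reproduce the plan's figure.** SE = 4 × √(2/64) = 0.707, and the noncentrality is 2/0.707 = 2.83. The noncentral t on 126 df gives power 80.15%, and 64 is the smallest number per arm that reaches 80%. The 95% CI half-width is 1.40 points. For attrition, 128/0.95 = 134.7, so 135 against the 136 stated. The sizing holds.

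**Step 2: adjust for k = 3 covariate terms.** The variance is multiplied by (1 − R²) × (1 + k/(n − k − 3)). The second factor is the price of chance imbalance in the covariates: 1 + 3/122 = 1.0246. Power uses 123 df.

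| Assumed R² | Variance factor | SE ratio (square root) | Power | Equivalent unadjusted N (128 ÷ factor) |
|---|---|---|---|---|
| 0 | 1.025 | 1.012 | 79.2% | 125 |
| 0.05 | 0.973 | 0.987 | 81.2% | 131 |
| 0.10 | 0.922 | 0.960 | 83.2% | 139 |
| 0.20 | 0.820 | 0.905 | 87.3% | 156 |

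Adjustment breaks even on variance at R² = 1 − 1/1.0246 = 0.024. If the Control Preferences Scale enters as three classes it takes two terms, so k = 4. Power is then 78.8%, 80.9%, 82.9% and 87.0%. Without the imbalance penalty, and with 4 df spent on covariates, the same R² values give 80.1%, 82.1%, 84.1% and 88.1%. Physician is in none of these figures.

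**Step 3: t-test against Wilcoxon.** Simulated 0-10 scores, 64 per arm, 20,000 trials per scenario. The distributions are assumed.

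| Beta-binomial scores, true difference 1 | t-test power | Wilcoxon power | Tests disagree |
|---|---|---|---|
| Means 7.5 v 8.5, SD 2 | 0.80 | 0.93 | 14% |
| Means 7.5 v 8.5, SD 2.2 and 2.0 | 0.76 | 0.87 | 12% |
| Means 7.0 v 8.0, SD 2.5 | 0.61 | 0.79 | 18% |

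Four other assumed shapes, with a 0.5 SD difference, gave disagreement in 3-10% of trials. There the t-test was slightly ahead (for example 0.70 v 0.65 on one ceiling-skewed shape). Which test has more power therefore depends on the shape of the scores and of the effect.

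With no true difference, each test alone rejects in about 5% of trials. Always taking the more favourable of the two rejects in 6.1-7.1% of the beta-binomial trials and 5.4-6.7% of those with the other shapes.

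**The case against.** **The unadjusted test is not an error.** A t-test in a randomised trial is valid, and step 1 shows that it meets its target. Covariates and a rule for choosing the test could also sit in an analysis plan that is not at hand. The first part stands: this is neither bias nor underpowering. The second stands only in part, because the protocol itself states the primary analysis and states it as an either/or.

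**The scores are only candidates.** A reader might infer that the protocol names known predictors of the primary outcome. It does not. Objective 6 sets out to establish predictors of the QPS's helpfulness, and its model uses dichotomised item 3, not the 0-10 score. The gain therefore rests on an unknown R², which may be near zero.

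**The false-positive rate.** A reader might infer that the open wording lets the significance level drift to 6-7%. That holds only if the more favourable p-value is always taken, and the protocol does not say that. Under one ordinary rule (Wilcoxon if a Shapiro-Wilk test on the residuals rejects normality, otherwise the t-test), the simulated rate was 4.7-5.2%. The inflation is a worst case, not a property of the plan.

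**A mean-based model can lose power.** In the beta-binomial scenarios the Wilcoxon beats the t-test by 11 to 18 points, more than the covariates are likely to return. This stands, so precision alone does not justify demoting the Wilcoxon. The reason to prefer the mean is that the trial is sized on it.

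**The two sets of figures use different SDs.** The adjustment table uses the protocol's SD of 4 and the beta-binomial scenarios use 2 to 2.5. At SD 2.5 the unadjusted power for 2 points is already 99.4%. The power gain then disappears, though the proportional narrowing of the interval remains.

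**Conclusion.** The point holds as a modest improvement, not as a flaw that invalidates the plan. Section F leaves the primary test, and with it the effect measure, open between two methods, only one of which matches the sample-size calculation. Naming one analysis is worthwhile even if R² is zero. Adjustment is a further, nearly free option: from 80% power unadjusted to about 79%, 81%, 83% or 87% at assumed R² of 0, 0.05, 0.10 or 0.20, given the protocol's SD of 4 and difference of 2.

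All of this applies to the 0-10 score. Section E9 defines the same outcome differently: "This will be assessed as the proportion of patients who agree or strongly agree that the information was helpful in the communication with their physician". If that binary definition stands, neither listed test suits it, and the adjusted model would be logistic or a risk-difference model. The two sections must be reconciled first.

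**What to change.** After reconciling sections E9 and F on the primary outcome, and if the 0-10 score is kept, replace the either/or in section F before any scores are seen:

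- **Primary analysis:** one linear model of the 0-10 score on arm. The prespecified covariates are pre-consultation state anxiety, the Cassileth preference for amount of detail and the Control Preferences Scale. Add physician as the stratification factor, with sparse physicians pooled or fitted as a random effect, since section E1 allows up to 20.
- **Report:** the adjusted mean difference with 95% CI and the p-value from this model.
- **Sensitivity analyses:** the unadjusted t-test and the Wilcoxon test.
- **Caregiver presence:** include it only if it is recorded before randomisation. Section E6 describes caregiver consent after the randomisation step and does not show when presence is captured.

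**Cost:** a few sentences in section F. The three baseline measures are already collected before randomisation and physician is already the stratification factor, so nothing new is asked of patients. If the covariates are not prognostic the CI is about 1% wider. If scores pile up strongly at the ceiling, the mean-based model may have less power than the Wilcoxon.

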**Secondary**

2. To compare caregivers' perception of helpfulness in communicating with their physicians between the QPS and the GIS.
3. To examine the level of patients' and caregivers' overall satisfaction with the consultation with the use of the QPS versus the GIS.
4. To examine physicians' views about the information material and overall satisfaction with the use of the QPS versus the GIS.

5. To explore how the use of QPS affects the average speaking time of patient or physician during the consultation visit.
6. To establish demographic and clinical predictors of patients' perception of helpfulness of a QPS
7. To examine the overall patients' preference between the QPS and GIS in an open label phase.
8. To compare the change in patient anxiety state with the use of the QPS versus the GIS.
9. To explore the factors underlying patients' preferences for the QPS or GIS.

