**8. The change in patient's anxiety state from pre-consultation to post-consultation.**

Patients' anxiety state will be measured using the **Spielberger State Trait Anxiety Inventory (Appendix A)**. This inventory consists of two 20 item self-report versions which measure situational (state) and general (trait) anxiety. Each item consists of a 4-point Likert response scale. The state anxiety version will be used in this study to measure participants' situational anxiety before and after the consultation visit. Total score ranges from 20 to 80, where a score indicates greater anxiety. The inventory's simplicity makes it ideal for evaluating individuals with lower educational backgrounds. It's been found to have high reliability( $r = 0.93$ ), internal consistency, and validity.

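### State anxiety (secondary objective 8) is tested on unadjusted change scores although the baseline score is taken before randomisation; adjusting for it would generally be more precise at almost no cost

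*Protocol*

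**What the plan says.** Secondary objective 8 in section A reads "To compare the change in patient anxiety state with the use of the QPS versus the GIS". Section E9, outcome 8, describes the instrument: "The state anxiety version will be used in this study to measure participants' situational anxiety before and after the consultation visit". Its total score runs from 20 to 80.

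The order of events is in section E6. The research coordinator is to "obtain patient's written consent and then ask him/her to complete the Spielberger State Trait Anxiety Inventory", together with two short preference questionnaires, and only after that comes "The patient will then be randomized to receive either the QPS" or the GIS. The inventory is repeated after the consultation.

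Section F fixes the analysis: "For the primary objective and secondary objectives 2, 3, 4, 8, two sample t-test or Wilcoxon rank sum test, whichever appropriate, will be used". For anxiety the variable compared is "d) the change in patient anxiety state scores before and after consultation between the QPS and the GIS". No covariate is named.

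A covariate-adjusted model between the arms appears in section F for objective 5 only, where a "general linear model will be applied to assess the effect of QPS on the average speaking time adjusting for clinically and/or statistically important factors". Section F closes with a general permission to use other methods where appropriate, which does not name baseline adjustment.

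**The concern.** When the outcome has been measured before randomisation, there are two usual ways to use that measurement. One is to subtract it, which forces a slope of 1 between pre and post scores. The other is to estimate the slope. Subtracting over-corrects whenever the true slope is below 1, and the over-correction adds noise to the treatment comparison. Section F commits the protocol to subtraction.

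What is at stake is the width of the interval for the difference in anxiety between the arms. The sample size was set for perceived helpfulness, and no power or precision is stated for anxiety. Whatever precision objective 8 has therefore comes from 128 patients and the analysis chosen. If the result shows no clear difference, its information lies in how narrow the interval is.

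**Working it through.** **Inputs from the protocol.** Randomisation is "in the ratio of 1:1 to reach 128 evaluable patients with 5% attrition rate", so 64 per arm, with 136 randomised. The test is two-sided at 0.05. The design difference is 2 with a standard deviation of 4, and this refers to helpfulness. For anxiety the protocol gives no standard deviation, difference or pre-post correlation.

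**The protocol's own figure.** A difference of 2 with SD 4 is a standardised difference of 0.5. The noncentral t calculation gives 63.8, so 64 per arm, with power 0.801. Allowing for 5% attrition, 128 / 0.95 = 134.7, so 135 against the stated 136. The sample size reproduces, but says nothing about anxiety.

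**Variance of the two analyses.** Let s be the common standard deviation of the pre and post scores and rho their correlation. Per patient:

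- Change score: 2s²(1 − rho)
- Adjusted for baseline (ANCOVA): s²(1 − rho²)
- Ratio, ANCOVA to change: (1 − rho²) / [2(1 − rho)] = (1 + rho)/2

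Estimating the slope multiplies the ANCOVA variance by about 1 + 1/(N − 4) = 1 + 1/124 = 1.008 at N = 128, hence the cost of about 0.8%.

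**Results over assumed correlations.** The last column is the power of ANCOVA at the difference for which the change-score t-test has 80%.

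| Assumed rho | (1 + rho)/2 | With slope cost | SE reduction | N needed with change scores to match 128 | ANCOVA power |
|---|---|---|---|---|---|
| 0.4 | 0.70 | 0.706 | 16.0% | 181 | 91.5% |
| 0.5 | 0.75 | 0.756 | 13.0% | 169 | 89.6% |
| 0.6 | 0.80 | 0.806 | 10.2% | 159 | 87.7% |
| 0.7 | 0.85 | 0.857 | 7.4% | 149 | 85.7% |
| 0.8 | 0.90 | 0.907 | 4.7% | 141 | 83.7% |
| 0.9 | 0.95 | 0.958 | 2.1% | 134 | 81.7% |

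The N column is 128 divided by the ratio with slope cost. Without that cost it would be 128 / 0.70 = 183 at rho 0.4 and 128 / 0.90 = 142 at rho 0.8. A simulation of 20,000 trials at N = 128 gave variance ratios of 0.707, 0.803 and 0.907 at rho 0.4, 0.6 and 0.8, in line with the formula.

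**Where the gain ends.** With equal standard deviations and the slope cost included, the two analyses break even at rho = 2 × 124/125 − 1 = 0.984. Above that, ANCOVA loses less than 1% of variance.

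**Unequal standard deviations.** The large-sample variance difference, change score minus ANCOVA, is

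(s_pre² + s_post² − 2·rho·s_pre·s_post) − s_post²(1 − rho²) = (s_pre − rho·s_post)².

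This is never negative. It is zero only when rho·s_post = s_pre, that is, when the regression slope of post on pre is 1. For example, a post SD of 1.25 times the pre SD with rho = 0.8 gives no gain.

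**The case against.** The strongest reply is that nothing here is an error. Objective 8 asks about change, outcome 8 defines change, and section F tests change. Under randomisation that test is unbiased and its type I error is valid. Anxiety is one of eight secondary objectives and has no precision target to miss. The correlation is unknown, and with both measurements taken around one clinic visit it could be high, where the gain is small. All of this stands. It settles the weight of the point but does not remove it, because in large samples adjustment is never less precise.

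A second reply is that the analysis plan may deal with covariates, and that section F leaves room for other methods. Section F nevertheless names the test for objective 8, and the closing permission commits to nothing.

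A reader might infer more than the protocol supports:

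- *That chance imbalance in baseline anxiety biases the result, since section E3 stratifies by physician only.* Such imbalance is already reflected in the standard error of the change score. It is the source of the lost precision, not a separate bias.
- *That a change score is always less precise unless the correlation is 1.* That holds only for equal standard deviations. The general condition is a slope of 1.
- *That objective 8 is the trial's main safeguard against raising anxiety.* No section says so. The Appendix F questionnaire also asks patients whether the material made them anxious (section E9, outcome 2, item e), and section E10 has a distress plan.
- *That the prompt sheet is known to contain end-of-life questions.* Appendix D is not shown. End-of-life issues appear in sections E7 and E9 as a category for coding the questions asked.
- *That a physician effect must be modelled here.* The argument and the arithmetic concern the baseline term only.

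**Conclusion.** The point holds as an efficiency improvement to a secondary analysis. For assumed correlations of 0.4 to 0.8, baseline adjustment lowers the variance by about 30% to 10% (29% to 9% after the slope cost). This rests on equal pre and post standard deviations, 128 patients with both scores, and a roughly linear relation between them. The direction of the gain does not need equal standard deviations; its size does. The figures compare ANCOVA with the t-test on change and do not quantify the Wilcoxon alternative. The planned test should not be described as invalid or biased.

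**What to change.** In section F, take objective 8 out of the list of two-sample comparisons and state that it will be analysed by a linear model of the post-consultation state anxiety score on arm and pre-consultation score, reporting the adjusted difference with its 95% confidence interval. Taking the change score as the outcome in the same model gives an identical arm effect, so the wording of objective 8 can stay. Keep mean change by arm as a descriptive summary, and name a rank-based analysis as a sensitivity check if the scores are skewed. A physician term is optional and not part of this point.

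The cost is a change of wording and one degree of freedom. No new data, visits or patients are needed. The change should be made before outcome data by arm are seen.
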